### Plans to give access to the full protocol, participant-level data, and statistical code {31c}

There is no current plan to give access to the full protocol, participant-level data, or the statistical code, however, the results will be published in peer-reviewed journals that may allow for statistical codes as supplementary.

## Oversight and monitoring

### Composition of the coordinating center and trial steering committee {5d}

The data will be monitored by the principal investigators, and access to the database is also handled by the principal investigator in collaboration with a data manager located in the Research Unit for Clinical Epidemiology, University of Southern Denmark, Odense, Denmark. The entire research group has access to the raw data. The research group will meet at least quarterly during the 1–2-year inclusion period and meetings will also be arranged on an ad hoc basis during the study period. The trial protocol has been registered at Clinical Trials (ClinicalTrials.gov — identifier: NCT04816812) after ethics approval was obtained.

### Composition of the data monitoring committee, its role and reporting structure {21a}

No data monitoring committee is set up for this trial. The data monitoring is done by the primary investigator and is independent of the sponsors. In Denmark, only trials approved by the Danish Medicines Agency, to investigate new drugs or changes in drugs, are mandatory to be monitored by The Regional GCP units (Good-Clinical-Pratice Units) in accordance with Danish legislation. This current trial on exercise does not involve any change in the patient's pharmacological treatment.

### Adverse event reporting and harms {22}

Adverse events are defined as side effects that are harmful due to the exercise intervention, e.g., severe musculoskeletal injuries that prevent participation or major increases in clinical symptoms related to IBD needing medical attention [48]. The included patients with IBD are considered to be at equal risk of any musculoskeletal injury as healthy patients start to exercise, and the exercise sessions will be supervised by trained health personnel. If patients in the project experience any adverse effects or harms due to the intervention or the study, the patient will be referred to the emergency department or the treating specialist physician at the gastroenterology department for an assessment and further treatment. All adverse events or harms are reported and recorded either by the research nurse or the physiotherapist during each exercise session in the research database. In case of any severe adverse event (SAE), e.g., potential life-threatening fall, the health professional will contact the emergency department/service as described by local in-hospital guidelines or by regular emergency service outside the hospital.

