## Interventions

### Explanation for the choice of comparators {6b}

We include patients with Crohn’s disease and ulcerative colitis with moderate disease activity as comparators and offer them one online lesson of 15–25 min on lifestyle guidance including general advice on healthy living. Specialized health personnel will present an educational video lesson. The patients in the comparison arm will receive the usual medical treatment with regular follow-up in the outpatient clinic. In this group, we will also monitor 7 days of physical activity level by accelerometry using the AX3 accelerometer [Axivity Ltd., Newcastle upon Tyne, UK] in weeks 0 and 12. The comparators have been chosen to represent the usual treatment and to help determine the efficacy of the intervention. Furthermore, all patients in the comparison arm will receive a wrist-worn heart rate monitor/fitness tracker (commercial) after completing a follow-up program identical to the patients in the intervention arm.

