### Interim analyses {21b}

There is no planned interim analysis, due to the short study period of 12 weeks. However, we will monitor any adverse events in relation to the intervention.

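### Adverse events are defined as harms due to exercise, so the comparator arm has none by construction and adverse event data cannot be compared between arms

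*Protocol article*

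**What the plan says.** The harms section {22} of the protocol article gives the definition: "Adverse events are defined as side effects that are harmful due to the exercise intervention". One of its two examples is "major increases in clinical symptoms related to IBD needing medical attention"; the other is severe musculoskeletal injury. Events are to be "reported and recorded either by the research nurse or the physiotherapist during each exercise session in the research database". Patients are referred for assessment if they "experience any adverse effects or harms due to the intervention or the study". The interim analyses section {21b} keeps the same limit: "we will monitor any adverse events in relation to the intervention".

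On the control side, section {6b} says: "The patients in the comparison arm will receive the usual medical treatment with regular follow-up in the outpatient clinic". Comparators also get one online lesson, but no exercise sessions. They receive their fitness tracker "after completing a follow-up program identical to the patients in the intervention arm". The article does not describe adverse event collection in this arm.

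Four other sections bear on the point:
- {12} lists HBI and SCCAI as secondary outcomes, and calprotectin and C-reactive protein as explorative ones.
- {20a} compares the specified outcomes between arms by intention to treat.
- {11b} ends trial participation when the responsible physician judges an increase in disease activity to be significant.
- {18b} asks withdrawn patients in both arms whether they would still answer questionnaires or attend visits.

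**The concern.** The definition requires a causal judgement before an event can be counted. For an injury during a session that may be workable. For IBD worsening it is not, because these patients enter with active disease of a kind that the background section {6a} describes as fluctuating, so some will worsen in either arm. Randomisation is what separates worsening caused by exercise from worsening that would have happened anyway, and that requires counting worsening in both arms by the same rule. Here it is counted in one arm only, and only after someone has attributed it to exercise.

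At stake is the part of the safety conclusion that rests on adverse events. A count from the exercise arm alone can be read as harm from exercise or as the background course of the disease, and the adverse event data cannot decide between these. The background section calls the earlier trials underpowered and the discussion expects the results to inform guidelines, so a usable safety comparison has real value. The primary IBDQ analysis is not affected.

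**Working it through.** **The plan's own figures.** The article gives no figure for harms. Its only calculation is for the IBDQ: a difference of 13.8 with SD 25, 80% power and alpha 0.05 (taken as two-sided) requires 52.5 per arm by the t-test, so 53 per arm and 106 in total. That reproduces {14} and has no bearing on this point. Two inputs are used from {14}: 75 patients per arm, and 33% dropout, which leaves 150 × 0.67 = 100.5, or about 50 per arm.

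**Step 1: can a comparator have an adverse event as defined?** {22} requires the harm to be due to the exercise intervention, and {6b} gives comparators none. The count is therefore zero whatever their true rate of worsening. The referral wording in {22} also covers harm due to the study, which could include a harm from a study procedure, but not a spontaneous flare.

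**Step 2: does the recording sentence change this?** The reference to exercise sessions may qualify only the physiotherapist, leaving the nurse free to record at other times. Even so, the definition governs what is recorded, and it still requires attribution to exercise.

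**Step 3: what goes uncounted?** The article gives no rate of worsening, so the rates here are assumptions. Expected number of comparators who worsen = 75 × p:
- p = 10%: 7.5
- p = 15%: 11.25
- p = 20%: 15
- p = 30%: 22.5

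None of these would be an adverse event under {22}.

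**Step 4: what would symmetric collection give?** With the same rate p in both arms, the 95% CI half-width for the risk difference is 1.96 × √(2p(1 − p)/n).

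| Assumed p | n = 75 per arm | n = 50 per arm |
|---|---|---|
| 10% | 0.096 | 0.118 |
| 15% | 0.114 | 0.140 |
| 20% | 0.128 | 0.157 |
| 30% | 0.147 | 0.180 |

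For p = 15% and n = 75: 1.96 × √(2 × 0.15 × 0.85/75) = 1.96 × 0.0583 = 0.114. With n = 50: 1.96 × 0.0714 = 0.140.

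Power is modest. For 10% against 20% at two-sided 0.05 it is 40% with 75 per arm and 29% with 50. For 10% against 30% it is 87% and 71%.

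**Step 5: do the scheduled measures fill the gap?** Only in part. HBI, SCCAI, calprotectin and C-reactive protein are taken in both arms, but they describe disease state at fixed visits. They do not record medical contact, treatment escalation or injury. Participation ends on significant worsening ({11b}) and later follow-up is only requested ({18b}), so the worst values may be missing. The outcomes text {12} puts disease scores at weeks 0, 4, 8 and 12, while the timeline table {13} marks them at weeks 0 and 12 only.

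**The case against.** The strongest counter-argument concerns how far the point reaches. A reader might infer that the trial cannot show whether exercise provokes IBD worsening, or that no unbiased safety comparison between arms is possible. The documents do not support either. Disease scores and inflammatory markers are measured in both arms without any attribution, under an identical follow-up programme, and are compared by intention to treat. Both the text and the timeline table have the scores at weeks 0 and 12. Withdrawn patients in both arms are asked to continue follow-up, which limits the loss of data from those who worsen, though it does not remove it.

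A reader might also infer that unblinded nurses and physiotherapists decide whether an event was due to exercise. {22} says only that they report and record. Patients are sent to the emergency department or the treating specialist for assessment, and the article does not say who decides relatedness. Nor is recording only at sessions a settled fact, given the other reading of the sentence.

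The illustration rests on an assumed rate, and the gain from symmetric collection is limited: about ±14 points rather than ±11 once the planned dropout is allowed for.

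Timing also counts. Inclusion was extended to 1 May 2023, so 12-week follow-up would end around late July 2023, before publication on 20 November 2023. New visit forms may come too late.

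All of this narrows the point. It leaves the definition as it stands: adverse events as defined have no control count.

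**Conclusion.** The point holds in a limited form. As {22} and {21b} are written, the comparator arm contributes no adverse events by construction, so adverse event data cannot be compared between arms. This matters most for IBD worsening needing medical attention, which can be expected in both arms. Whether exercise affects disease activity can still be examined through the scheduled scores and markers, with the gaps described in step 5.

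The size depends on a worsening rate that the article does not give. At an assumed 15% in both arms, about 11 of 75 comparators would worsen uncounted. Symmetric collection would replace no comparison with an imprecise one that does not depend on attribution: a half-width of about 11 points at 75 per arm and 14 at 50. Over assumed rates of 10% to 30% the half-width runs from about 10 to 18 points. This is a rule that the article states, not a detail left to a fuller document. It should be changed, but it does not threaten the primary analysis.

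**What to change.** Reword {22}, and {21b} to match, so that an adverse event is any untoward medical occurrence in either arm, with relatedness to exercise recorded as a separate field and the person who judges it named.

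Ascertain four items by the same rule in both arms: IBD worsening needing medical attention, treatment escalation, hospital contact and musculoskeletal injury. Use the existing contacts at weeks 4, 8 and 12. Where those have passed, use the medical records, since the consent described in {26b} already allows health status to be obtained from them to monitor quality and safety.

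Report risk differences with 95% confidence intervals by randomised arm for these items. List session-recorded events separately, because only one arm has sessions. Reconcile {11b} with {18b} on what data are collected after participation ends, and {12} with {13} on when disease scores are taken.

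The cost is one further form at contacts that already exist, or a record review in both arms, plus revised wording. More events will be reported, many of them unrelated to exercise, and the relatedness field lets a reader see that.

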### Frequency and plans for auditing trial conduct {23}

We plan to audit the trial data every month. The primary investigator and one member of the research group will oversee the data including any adverse events to be reported.

### Plans for communicating important protocol amendments to relevant parties (e.g., trial participants, ethical committees) {25}

All modifications of the protocol will be reported to the regional ethics committees, and all changes will be reported in the participation information. The principal investigator is responsible for updating the online registration on trials.gov.

### Dissemination plans {31a}

We will publish the data in peer-reviewed scientific journals, present at international research conferences, and reach out to local patient associations.

## Discussion

This trial is the first trial trying to include a large number (*n* = 150) of patients with IBD and moderate disease activity in order to explore the effect of an exercise intervention. We have chosen this number of patients to be able to evaluate meaningful effects in our specified outcomes. We expect that the results will be helpful in future clinical guidelines, and add highly relevant knowledge on the effect of exercise that may guide patients in clinical practice and may provide a new patient-active disease management approach. The current evidence on the effects of exercise on IBD is inconsistent with few clinical trials with a sufficient number of included patients.

The randomized controlled study design applied in our trial is a strength. Another strength related to this trial is that the protocol has been developed with guidelines from the SPIRIT and PREPARE guidelines, [30, 49] and that the protocol is being published to enhance clearance and transparency. Further strengths in the development of the protocol are that patient representatives were involved to help inform plus guide the selection of outcome of interest, design exercise regime using the FITT principles, [26] and online lifestyle presentation. Another strength is that the measurements in the trial are based on validated questionnaires in combination with objective repeated measurements, e.g., accelerometry, blood samples, and fecal samples that are stored in a biobank to evoke current and future relevant research.

Our trial has some limitations. Due to the nature of the exercise intervention blinding the research nurses, physiotherapists, and participants is not an option. Limitations according to the recruitment of participants do exist because we focus on patients with mild to moderate disease activity. These patients may be more cautious to participate due to symptoms or because of the possibility of not being randomized to the intervention or not being able to participate in the intervention because of their schedule. Another limitation of the trial is that we have not planned follow-up after week 12. However, we have chosen not to plan a long-term follow-up because we do not yet clearly know the short-term effect of exercise, which is the focus of this trial. Selection bias may be of concern when conducting a trial on exercise, and this may influence the generalizability of the study.

## Trial status

Protocol version 4 — 25 November 2021. Recruitment started on 15 November 2021 and approximately ends on 15 November 2022. Inclusion extended to 1 May 2023.

## Data Availability

The principal investigator and the research group will have access to the final trial dataset. Access to the data is limited by Danish legislation, and patient data may not be directly available to other parties. The research group does not have any plans to share data currently.

## Abbreviations

GCP: Good Clinical Practice
HBI: Harvey Bradshaw Index
IBD: Inflammatory bowel disease
IBDQ: Inflammatory Bowel Disease Questionnaire
ITT: Intention-To-Treat
MCID: Minimum Clinical Important Difference
PP: Per-Protocol
SCCAI: Simple Clinical Colitis Activity Index
